#### *Aim 4 Power*

Based on available data, we anticipate 2,170 adolescents will be arrested per year from the 8 counties. The county-specific (i.e., cluster-specific) estimated annual arrests/referrals is shown below.

| County  | #referrals | year #referrals
was reported |
|----------------|-------------------|-----------------------------------------|
| 1              | 325               | 2017                                    |
| 2              | 190               | 2017                                    |
| 3              | 290               | 2017                                    |
| 4              | 328               | 2017                                    |
| 5              | 164               | 2017                                    |
| 6              | 706               | 2017                                    |
| 7              | 40                | 2018                                    |
| 8       | 127        | 2018                             |
| Total per year | 2170              |                                         |

However, we acknowledge some youth will be placed out of the home (DOC and residential placement). Additionally, some youth will migrate out of the community (which will be assessed by address data from state-wide databases; INPC, Medicaid, & DCS). Thus, we conservatively estimate that roughly 70% of 2,170 (i.e., 1,519) adolescent arrestees per year will be available in-home in the community from the 8 counties (4,557 total over 36 months of implementation which includes 30 months of intervention plus 6 prior months in which all cohorts experience the control condition under the baseline period). Based on an annual 30% recidivism rate, we estimate that 30% (1,367) of the projected 4,557 arrests for this trial will represent repeated arrests from the same youth, yielding an estimated 3,190 unique youth available in the administrative data over the 36 months of the primary outcome measurement period. We will actually collect and use administrative data for 5 years (not just 6 months) prior to the start of intervention; however, to be conservative, the step wedge power calculation assumed only 6 months of prior baseline administrative data (i.e., 36 months of primary administrative measurement). Additionally, although all data (including multiple arrests for the same youth) will be used in the model, to be conservative for the power analysis, we assumed that the maximum sample size available for the power calculations is the number of unique youth (3,190).

Our design has 8 counties (i.e., clusters). A projected maximum available sample size of 3,190 unique youth, over the 36-month primary evaluation period, yields: (1) 531 youth per 6-month time period, (2) an average of 398 maximum youth per cluster over 36 months (*M* in the Step Wedge Design), and (3) an average of 66 youth per cluster per 6-month time period (*m* in Step Wedge design).

We used the PASS software to calculate power for a test of two poisson rates (control condition event rate vs treatment condition event rate) in a cluster-randomized step wedge design. Our step wedge design is an "incomplete design" in which a different number of clusters (i.e., counties) start the intervention at each step. Given 8 clusters and practical considerations, we decided to initiate intervention for 3 clusters in cohort 1, then in the next step another 3 clusters in cohort 2, and then in the next step another 2 clusters in cohort 3.

We input the following customized design matrix into the PASS software. The timeline, shown elsewhere in this application, is displayed in 3-month increments to show specific details such as the 3 months of dissemination at the end of study. For the step wedge design matrix, each time period

represents a 6-month time interval because the administrative outcome data will be measured every 6 months, and the cohorts will also be started on intervention in 6-month steps of our step wedge design.

Step Wedge Design Matrix (Incomplete Design: K = 8 Clusters, S = 5 Steps, T = 6 Times Periods)

|        |                | Time (6-month intervals) |        |         |          |          |          |
|--------|----------------|--------------------------|--------|---------|----------|----------|----------|
|        |                | 1                        | 2      | 3       | 4        | 5        | 6        |
|        |                | Intervention Months      |        |         |          |          |          |
| Cohort | County Cluster | -6 to 0                  | 1 to 6 | 7 to 12 | 13 to 18 | 19 to 24 | 25 to 30 |
| 1      | 1              | 0                        | 1      | 1       | 1        | 1        | 1        |
| 1      | 2              | 0                        | 1      | 1       | 1        | 1        | 1        |
| 1      | 3              | 0                        | 1      | 1       | 1        | 1        | 1        |
| 2      | 4              | 0                        | 0      | 1       | 1        | 1        | 1        |
| 2      | 5              | 0                        | 0      | 1       | 1        | 1        | 1        |
| 2      | 6              | 0                        | 0      | 1       | 1        | 1        | 1        |
| 3      | 7              | 0                        | 0      | 0       | 1        | 1        | 1        |
| 3      | 8              | 0                        | 0      | 0       | 1        | 1        | 1        |

For the PASS input parameters, we assumed an intra-class (i.e., intra-cluster) correlation coefficient of 0.01, a two-sided test of the rate ratio (intervention vs control conditions), and an alpha of 0.05. We calculated power for 4 different hypothesized poisson rate ratios (effect size) ranging from 1.25 to 1.40 by .05. Results show that a total sample size of 2,400 youth (i.e., average of 300 unique youth per cluster with an average of 50 youth per cluster per 6-month time period) will provide 80% to 99% power for detecting population rate ratios, for various outcomes derived from administrative data described elsewhere, ranging from 1.25 to 1.40 (See PASS Report below). Thus, the available total sample size of 3,190 unique youth (i.e., average of 398 unique youth per cluster with an average of 66 youth per cluster per 6-month time period) will provide more than ample power (e.g., exceeding 80% power for a rate ratio of 1.25). In addition, the actual analysis will include youth with multiple arrests which will increase power further.

#### PASS Results Report for Power for Comparing Poisson Rates for Aim 4

Design Type: Incomplete (Custom)

Test Statistic: Wald Z-Test

Hypotheses:  $H_0: \lambda_1/\lambda_2 = 1$  vs.  $H_1: \lambda_1/\lambda_2 \neq 1$

|       | Design | Clusters | Cluster Size | Sample Size | Trt Rate    | Ctrl Rate   | Ratio | ICC   | Alpha |
|-------|--------|----------|--------------|-------------|-------------|-------------|-------|-------|-------|
| Power | S/T/R  | K        | M/m          | N           | $\lambda_1$ | $\lambda_2$ | RR1   |       |       |
| 0.80  | 5/6/1  | 8        | 300/50       | 2400        | 1.25        | 1.00        | 1.25  | 0.010 | 0.050 |
| 0.91  | 5/6/1  | 8        | 300/50       | 2400        | 1.30        | 1.00        | 1.30  | 0.010 | 0.050 |
| 0.97  | 5/6/1  | 8        | 300/50       | 2400        | 1.35        | 1.00        | 1.35  | 0.010 | 0.050 |
| 0.99  | 5/6/1  | 8        | 300/50       | 2400        | 1.40        | 1.00        | 1.40  | 0.010 | 0.050 |

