### Synopsis

Indiana, a rural Midwest state, ranks 14th nationally in drug overdose deaths. From 2016 to 2017, Hoosiers experienced the 3rd largest increase (22.5%) in overdose deaths, evidencing continuing need for intervention to reduce drug-related fatalities. Youth involved in the juvenile justice system (YJJ) bear a disproportionate burden of the addiction crisis. YJJ substance use (SU) is extremely prevalent, with a third of YJJ meeting criteria for a substance use disorder (SUD). Our research has shown that YJJ die at 1.5 times the rate of youth who have never been arrested, and a leading cause of YJJ death is drug overdose. By targeting YJJ in rural counties, our research team seeks to address the national addiction crisis at its epicenter.

Despite their high need for SU services, and the proliferation of evidence-based interventions to reduce SU, YJJ are rarely connected to needed, high-quality SU care. A cascade of care model highlights implementation gaps in YJJ achieving the full continuum of SU care (i.e., SUD risk identification, treatment referral, treatment initiation, and treatment engagement). YJJ on community supervision/probation face a unique problem accessing SU services; while the courts or probation may identify YJJ need for SU care, YJJ must receive care through healthcare agencies in the community. The primary goal of our proposed project, Alliances to Disseminate Addiction Prevention and Treatment (ADAPT) is to address this and other implementation gaps in the Cascade for YJJ. We will accomplish our goal by creating alliances between the juvenile justice system (JJ) agencies and community mental health centers (CMHCs) in eight Indiana counties.

ADAPT takes a two-pronged approach. First, we will employ a Learning Health System (LHS) to develop collaborative alliances between JJ agencies and CMHCs, organizations that traditionally operate independently. Second, we will present local Cascade data during continuous quality improvement cycles within the LHS alliances. By offering agency representatives an opportunity to view and discuss, for example, the local rate at which YJJ with SUD risk are initiating CMHC SU services, we will facilitate development of tailored, local solutions to improve the Cascade for each county's YJJ.

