#### *Aim 4 Comparative Effectiveness Analyses*

##### *Aim 4 Analyses*

We will use standard step wedge analytic methods (see citations in reference list for PASS report). We will use repeated measures Poisson models to compare control vs LHS intervention conditions on the response rate ratio for the SU cascade outcomes and the opioid related outcomes. The Poisson or zero-inflated Poisson regression models will be performed using SAS GENMOD to fit repeated measures generalized linear models (GLIM) with generalized estimating equations (GEE) to account for the fact that event data for youth will be measured repeatedly over time and to account for the correlation due to within-organization clustering. The outcome data will be entered into the model as event counts for every 6-month period of the 36 months of implementation (6 months of control condition for all clusters, then 30 months of intervention), reported separately for each arrest record. Multiple arrests for the same youth will be used in the model. In the power analysis (described below), we conservatively based the power calculations on the number of unique youth arrested. The actual analysis will use a random effect to incorporate data from youth who have multiple arrests.

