The amount of time (in days) exposed to the implementation for each adolescent arrestee will be accounted for in the rate ratio by defining the "offset" variable as the natural log of the number of days of exposure for every 6-month period of implementation. The primary denominator will be the number of arrested youth in the rolling intake cohort (e.g., % referred as a percentage of the number in the arrestee intake cohort). For some outcomes, another separate outcome will be derived and analyzed using a smaller denominator (e.g., % referred as a percentage of YJJ in need of treatment). The denominator for % in need (i.e., % screened positive) will be YJJ screened. The denominator for the % engaged will be the YJJ initiated. Because some youth will have multiple arrests, they could also have multiple screenings. In addition, for a single arrest and single screening, there could be multiple referral events over any 6-month period; for a single referral, there could be multiple treatment initiation events; and for a single treatment initiation, there could be multiple occurrences of an engaged event (i.e., 2+ behavioral health visits within 30 days after initiation) over any 6-month period. Therefore, the model will capture these multiple events as counts for every 6-month period.

Covariate-by-6-Month-Period interactions will be tested to determine whether the outcome response rates changed differently over time for different values of covariates.

In addition, youth-level covariates (demographics and health visit data) will also be included as predictors.

In the next step of the model, we will include organizational-level (i.e., county-by-system [JJ and CMHC]) survey predictors including staff characteristics (JPO age, sex, and race/ethnicity, time in current position, highest/type degree, number of previous positions, salary, caseload size, job (dis)satisfaction rating, turnover intentions, and burnout rating), implementation variables (readiness,

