### Summary Statements

A sample of 8 clusters in an incomplete (or custom) stepped-wedge cluster-randomized design with 6 time periods (including the baseline), 5 steps, and an average of 300 subjects per cluster with an average of 50 subjects per cluster per time period (for a total sample size of 2400 subjects) achieves 80% power to detect a ratio of 1.25. The treatment event rate is assumed to be 1.25 under the alternative hypothesis. The control event rate is 1.00. The test statistic used is the two-sided Wald Z-Test. The ICC is 0.010, and the significance level of the test is 0.050.

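### The Aim 4 power table assumes plain Poisson variance, which does not match the referral and initiation counts over all arrestees that the plan will analyse

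*Protocol*

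**What the plan says.** The Aim 4 Power section states: "We used the PASS software to calculate power for a test of two poisson rates". The Summary Statements of its PASS report give the inputs: "The treatment event rate is assumed to be 1.25 under the alternative hypothesis. The control event rate is 1.00". They add a Wald test, two-sided at the 5% level, and an intra-cluster correlation of 0.01. The result is that "50 subjects per cluster per time period (for a total sample size of 2400 subjects) achieves 80% power to detect a ratio of 1.25". Across ratios 1.25 to 1.40, 2,400 youth "will provide 80% to 99% power for detecting population rate ratios". The section then says that the 3,190 unique youth expected give power above 80% at 1.25, which it describes as more than sufficient. No dispersion or excess-zero input appears.

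The Aim 4 Analyses section describes the data differently. "The Poisson or zero-inflated Poisson regression models will be performed using SAS GENMOD", with GEE for repeated data on youth and for clustering. One screening may lead to several referrals, one referral to several initiations, and so on; all are entered as counts per 6-month period. "The primary denominator will be the number of arrested youth in the rolling intake cohort". Some outcomes also get a smaller denominator (referral among youth in need), and engagement uses youth who initiated.

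The Synopsis describes substance use in this population "with a third of YJJ meeting criteria for a substance use disorder (SUD". The text after the Aim 4 PASS report says that PASS treats the design as cross-sectional, that the trial is mainly a cohort with repeated measurement, and that the cross-sectional assumption is therefore conservative.

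**The concern.** A Poisson count has variance equal to its mean. Two features of the planned outcome push the variance above that. Many arrestees have no treatment need and so little chance of a referral or initiation, while those with need can have several. The ICC of 0.01 covers variation between counties and does not absorb this excess between youth. A marginal rate ratio over all arrestees carries the excess in full.

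The stated power, the detectable ratio and the conclusion that power is ample all depend on the variance entered. If it is too small for referral and initiation, all three are too favourable for those outcomes, even if the assumed rate of 1.00 is accepted.

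**Working it through.** **Inputs.** From the step wedge design matrix: 8 counties, 6 periods, with 3, 3 and 2 counties crossing over at periods 2, 3 and 4. From the PASS report: rates 1.00 and 1.25, ICC 0.01, two-sided alpha 0.05, m = 50 youth per county per period (2,400). For 3,190 youth, m = 3,190/48 = 66.5.

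**Formula.** Hussey-Hughes variance of the treatment effect with fixed period effects:

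Var = I·s²·(s² + T·τ²) / [(I·U − W)·s² + (U² + I·T·U − T·W − I·V)·τ²]

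Here I = 8 and T = 6. U = 33 treated cells, W = 237 (sum of squared column totals) and V = 141 (sum of squared row totals), so the two brackets are 27 and 123. s² is the within-county variance divided by m, and τ² is the between-county variance. Power = Φ(0.25/SE − 1.96).

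**The plan's figure.** The average rate is (1.00 + 1.25)/2 = 1.125, taken as the total variance. Then τ² = 0.01 × 1.125 = 0.01125 and s² = 0.99 × 1.125/50 = 0.022275.

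Var = 8 × 0.022275 × (0.022275 + 0.0675) / (27 × 0.022275 + 123 × 0.01125) = 0.015998/1.985175 = 0.00806, so SE = 0.0898.

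Power = Φ(2.785 − 1.960) = 79.5%. The other three ratios give 91.1%, 96.8% and 99.1%, against the printed 91%, 97% and 99%. At m = 66.5, SE = 0.0784 and power is 89%. So the table reproduces with variance equal to mean.

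**Adding structural zeros.** If a share p0 of youth cannot have the event and the overall mean μ is kept, the variance is μ + μ² × p0/(1 − p0). At p0 = 2/3 and μ = 1.125 this is 1.125 + 1.2656 × 2 = 3.656, or 3.25 times the variance entered. The lower figure in each range below applies the ICC of 0.01 to the inflated variance; the upper keeps τ² at 0.01125.

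| p0 | 2,400 youth | 3,190 youth |
|---|---|---|
| 0 | 80% | 89% |
| 0.2 | 69-70% | 80-81% |
| 0.3 | 63-64% | 74-75% |
| 0.5 | 48-50% | 59-61% |
| 2/3 | 34-36% | 42-45% |

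A simulation of zero-inflated counts (4,000 runs, ICC applied to the inflated variance) gave 80% at p0 = 0 and 35% at p0 = 2/3 with m = 50, and 42% at p0 = 2/3 with m = 66. At 3,190 youth, power at a ratio of 1.25 drops below 80% once p0 passes about 0.2. The ratio detectable with 80% power at 3,190 youth moves from 1.22 to about 1.41 at p0 = 2/3.

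**Dependence on the rate.** At 3,190 youth and p0 = 2/3, a control rate of 0.3 takes power from 42% (plain Poisson) to 28%, and a rate of 0.1 from 17% to 15%. The loss from dispersion is smaller there because plain Poisson power is already low.

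**Repeated measurement.** Assume the same unique youth, entering evenly over the six periods, each followed for two 6-month periods where the calendar allows, with p0 = 2/3.

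| Two periods per youth | 2,400 youth | 3,190 youth |
|---|---|---|
| Zero status fully stable, youth correlation modelled (GLS) | 85% | 93% |
| Half the excess variance stable, GLS | 65% | 76% |
| Zero status fully stable, youth correlation ignored in the weights | 60% | 72% |

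With three periods the corresponding figures are 96% and 99%, 77% and 87%, and 72% and 84%.

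**The case against.** The strongest objection is the cohort design. If excess zeros come from a stable trait such as absence of a disorder, much of that variance cancels when the same youth is compared before and after crossover. With two periods per youth, fully stable zeros and correlation modelled at youth level, power returns to 85% at 2,400 and 93% at 3,190. This stands as a possibility. It does not rescue the printed table, because the protocol states neither the follow-up per youth nor the working correlation, and with youth correlation ignored the same two periods give 60% and 72%.

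A reader might infer that the trial's true power is 36%. The documents do not support that:

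- It equates prevalence of disorder with the share able to have an event. The Synopsis figure is background, and the cascade runs on a positive screen for risk, so youth without a diagnosis may be referred.
- It keeps the overall mean at 1.00 with two thirds zeros, which requires 1.00/(1/3) = 3 events per at-risk youth per 6 months.
- It uses 2,400 youth, whereas the plan relies on 3,190.
- The zero-inflated model is named only as an alternative to the Poisson.

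Nor do the zero-inflation figures extend to engagement or to referral among youth in need, since youth without need are then largely outside the denominator. Nor is the printed table an arithmetic error: it reproduces.

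**Conclusion.** The point holds as a mismatch between the variance assumed for power and the counts to be analysed. For referral and initiation over all arrestees, the table's 80% at a ratio of 1.25 holds only without excess variance between youth. On the plan's own cross-sectional basis at a control rate of 1.00, a structural-zero share of about 20% already brings the 3,190 youth down to the 80% that the plan says they exceed. Larger shares cost much more, down to the two-thirds scenario in the table above.

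The size is conditional on three things that the protocol does not give: the zero fraction, the event rate per outcome, and the number of periods per youth together with how their correlation is modelled. Depending on these, the loss may be fully recovered or may be large. An unconditional statement that power is ample is therefore unsupported for these outcomes.

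**What to change.** Rerun the Aim 4 power table with variance μ + μ² × p0/(1 − p0) and a control rate for each outcome. Take p0 and the rate from the five pre-study years of records that the trial already plans to collect, or show a range of p0. State the assumed number of 6-month periods per youth and how correlation within youth is handled. Then restate power and the detectable ratio, and either make the claim of ample power conditional on those inputs or withdraw it for the arrestee-denominator outcomes.

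The cost is a recalculation and revised wording. No participants are added; the stated power may become less favourable.

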#### Report Definitions

S is the number of steps in the study design.  $S = T - 1$ .

T is the number of time periods in the study, including the baseline.  $T = S + 1$

R is the number of times that each row of the custom design pattern matrix is replicated.

K is the total number of clusters to be randomized.

M is the average number of subjects per cluster.

m is the average number of subjects per cluster per time period.  
N is total sample size from all clusters and time periods combined.  
 $\lambda_1$  is the average treatment event rate per unit time, assuming the alternative hypothesis.  
 $\lambda_2$  is the average control, standard, reference, or baseline event rate per unit time.  
 $RR_1 = \lambda_1/\lambda_2$  is the rate ratio assuming the alternative hypothesis ( $H_1$ ).  
ICC is the intra-cluster correlation coefficient.

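### Aim 4 power was computed only at a control rate of 1.00 event per youth-period, so the 80% claim does not carry over to recidivism or to rare opioid outcomes

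*Protocol*

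**What the plan says.** All references are to the protocol. The Aim 4 Power section sets "a two-sided test of the rate ratio (intervention vs control conditions), and an alpha of 0.05", with an intra-cluster correlation of 0.01, and examines rate ratios of 1.25, 1.30, 1.35 and 1.40. The PASS table gives power of 0.80, 0.91, 0.97 and 0.99 for 8 counties, 6 periods and 50 youth per county per period (2,400 in all). The Summary Statements after that table say "The control event rate is 1.00" and "The treatment event rate is assumed to be 1.25 under the alternative hypothesis". The Report Definitions describe the control rate only as one that "is the average control, standard, reference, or baseline event rate per unit time".

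The section extends the result to the various administrative outcomes and concludes that the projected 3,190 youth "will provide more than ample power (e.g., exceeding 80% power for a rate ratio of 1.25" (the parenthesis closes there). No reason is given for the rate of 1.00, and no other rate is tried.

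Elsewhere, Aim 4 Analyses enters outcomes as event counts per six-month period and states: "The primary denominator will be the number of arrested youth in the rolling intake cohort". Aim 4 Power discounts repeat arrests "Based on an annual 30% recidivism rate". The Outcome Measures table lists cascade, recidivism and opioid-related outcomes as primary.

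**The concern.** At a fixed ratio, the information in a Poisson comparison grows with the expected number of events. A ratio of 1.25 therefore has no single power; it has one for each control rate. The protocol gives one power for outcomes whose rates must differ widely, at a rate well above the one outcome rate that it states itself.

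Direction matters too. The Synopsis and Outcome Measures expect recidivism and opioid-related events to fall, so the relevant ratio is below 1, and none was examined.

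At stake is how a null result is read. If recidivism or opioid outcomes show no significant difference, a protocol that records ample power invites the reading that an effect of that size was ruled out.

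**Working it through.** **Inputs.** Two-sided alpha 0.05, ICC 0.01, and 50 youth per county-period (stated power) or 66 (the protocol's figure for 3,190 youth), all from Aim 4 Power. The design matrix has 3, 3 and 2 counties starting in periods 2, 3 and 4 of six six-month periods.

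**Formula.** Hussey-Hughes variance for a cross-sectional stepped wedge. With control rate λ and ratio r, take the total variance as λ(1+r)/2 and factor it out. Then s = 0.99/m, t = 0.01, I = 8, T = 6. From the matrix:
- U = 33 (treated cells)
- W = 0+9+36+64+64+64 = 237 (squared column sums)
- V = 3×25+3×16+2×9 = 141 (squared row sums)

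V0 = I·s(s+T·t) / [(IU−W)s + (U²+ITU−TW−IV)t] = 8s(s+0.06) / (27s+1.23)

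Power = Φ( |r−1|√λ / √(V0(1+r)/2) − 1.96 )

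**Reproducing the plan.** m = 50: s = 0.0198, V0 = 0.01264/1.7646 = 0.00716. At λ = 1 and r = 1.25, 0.25/√(0.00716×1.125) = 2.785 and Φ(0.825) = 0.795. The four ratios give 0.795, 0.911, 0.968 and 0.991, against the stated 0.80, 0.91, 0.97 and 0.99. The match also settles the unit: each youth in a cell contributes 1.00 expected event, and a cell is six months.

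**At 3,190 youth.** m = 66: s = 0.015, V0 = 0.009/1.635 = 0.005505. At r = 1.25 the multiplier is 0.25/√(0.005505×1.125) = 3.177. At r = 0.80 it is 0.20/√(0.005505×0.9) = 2.841. Each is multiplied by √λ.

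Break-even for 80% at 1.25: λ = (2.802/3.177)² = 0.78.

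Recidivism of 30% a year is 0.30/2 = 0.15 per six months, or −ln(0.70)/2 = 0.178 at constant hazard.

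| Control rate per youth per six months | Basis | Power at 1.25 | Power at 0.80 | Ratio above 1 for 80% |
|---|---|---|---|---|
| 1.00 | PASS input | 0.89 | 0.81 | 1.22 |
| 0.78 | break-even | 0.80 | 0.71 | 1.25 |
| 0.33 | illustrative cascade rate | 0.45 | not the expected direction | 1.39 |
| 0.178 | 30% a year, constant hazard | 0.27 | 0.22 | 1.56 |
| 0.15 | 30% a year, halved | 0.23 | 0.20 | 1.61 |
| 0.05 | assumed, opioid | 0.11 | 0.09 | 2.17 |
| 0.01 | assumed, opioid | 0.05 | 0.05 | 4.42 |

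**More favourable data assumptions, ratio 1.25, recidivism at 0.15 to 0.178.**
- Five baseline years (ten pre-periods) alone: 0.26 to 0.30.
- All 4,557 arrests (4,557/48 ≈ 95 per cell): 0.31 to 0.36.
- All arrests plus five baseline years: 0.35 to 0.40.
- Youth accumulating from 66 to 396 per cell, independent and without loss: 0.50 to 0.57.

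Using 3,190/48 = 66.5 per cell and a rate of 0.18 moves the upper ends by at most 0.01 (0.23 at ratio 0.80, 0.58 for the accumulating cohort).

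**County sizes.** With cells proportional to the referral table in Aim 4 Power (40 to 706 a year), rate 1.00 and ratio 1.25, over all 560 allocations of counties to cohorts: mean power 0.76 (range 0.65 to 0.82) at 2,400 youth, and 0.86 (0.76 to 0.91) at 3,190.

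**The case against.** The strongest reply is that the calculation was a deliberate simplification. The text after the PASS report says that the design is mainly a cohort with repeated measurement, and Aim 4 Power adds five baseline years and repeat arrests. This stands in part. In the optimistic accumulating scenario, an outcome at 0.33 events per youth-period reaches 0.83, so some cascade counts could be adequately powered. The same scenario leaves recidivism at 0.58 or below and opioid events, at the assumed rates, at 0.07 to 0.20.

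Several stronger readings are tempting, and the protocol does not support them:
- A reader might infer that a rate of 1.00 means every arrested youth already has the event. Aim 4 Analyses counts multiple screenings, referrals, initiations and engagements, so 1.00 is a mean count, not a prevalence of 100%.
- A reader might infer that cascade power is shown to fall short. The Synopsis figure, "with a third of YJJ meeting criteria for a substance use disorder (SUD", is background prevalence, not a control rate for any outcome. No baseline rate is given for referral, initiation or engagement, so 0.33 is only an illustration.
- A reader might infer that unequal counties defeat the claim at 3,190 youth. They do not on average (mean 0.86); they undercut only the 2,400-youth figure.

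Two limits also stand. Aim 4 Analyses names cascade and opioid outcomes for the Poisson comparison, so recidivism comes under the power claim only through its general wording and its listing as primary. The 30% figure was given to discount repeat arrests, and turning it into a six-month rate is an approximation, hence the range.

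**Conclusion.** The point holds. The PASS figures are correct for what was entered; the fault is carrying one unjustified control rate to every outcome. The claim of more than 80% power at 1.25 is true with 3,190 youth only for outcomes near 0.8 or more events per youth per six months. For recidivism, at the protocol's own rate, power is 0.23 to 0.27 (0.20 to 0.23 for a ratio of 0.80), and no data assumption tried brings the 1.25 figure above about 0.58. For opioid outcomes the size rests on an assumed 0.01 to 0.05, giving 0.05 to 0.11; the protocol has no figure. For cascade outcomes the answer is open: 0.45 at an illustrative 0.33 in cross-section, up to 0.83 if youth accumulate. All figures assume ICC 0.01 and the design matrix as stated and, apart from the county-size check, equal counties.

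**What to change.** Replace the single claim in Aim 4 Power with a table that has one row per primary administrative outcome:
- the control rate per youth per six months, from the pre-study administrative records;
- the expected direction;
- the power, or the ratio detectable with 80% power, at 3,190 youth with the county sizes already tabulated.

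Limit the statement of 80% at 1.25 to outcomes with roughly 0.8 or more events per youth-period, and remove the description of power as ample. State that recidivism will be estimated with low power, and opioid outcomes too if they prove as rare as expected. If the cohort structure or the five baseline years are relied on, build them into the calculation.

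The cost is a rerun of the power table and a less favourable statement. No more youth are needed, and neither the design nor the planned analysis changes.
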